# Gender-Specific Combination HIV Prevention for Youth in High-Burden Settings: The MP3 Youth Observational Pilot Study Protocol

**DOI:** 10.2196/resprot.5833

**Published:** 2017-03-08

**Keywords:** HIV, combination prevention, Kenya, youth, PrEP, VMMC, mobile health, family planning, cash transfer, biometrics

## Abstract

**Background:**

Nearly three decades into the epidemic, sub-Saharan Africa (SSA) remains the region most heavily affected by human immunodeficiency virus (HIV), with nearly 70% of the 34 million people living with HIV globally residing in the region. In SSA, female and male youth (15 to 24 years) are at a disproportionately high risk of HIV infection compared to adults. As such, there is a need to target HIV prevention strategies to youth and to tailor them to a gender-specific context. This protocol describes the process for the multi-staged approach in the design of the MP3 Youth pilot study, a gender-specific, combination, HIV prevention intervention for youth in Kenya.

**Objective:**

The objective of this multi-method protocol is to outline a rigorous and replicable methodology for a gender-specific combination HIV prevention pilot study for youth in high-burden settings, illustrating the triangulated methods undertaken to ensure that age, sex, and context are integral in the design of the intervention.

**Methods:**

The mixed-methods, cross-sectional, longitudinal cohort pilot study protocol was developed by first conducting a systematic review of the literature, which shaped focus group discussions around prevention package and delivery options, and that also informed age- and sex- stratified mathematical modeling. The review, qualitative data, and mathematical modeling created a triangulated evidence base of interventions to be included in the pilot study protocol. To design the pilot study protocol, we convened an expert panel to select HIV prevention interventions effective for youth in SSA, which will be offered in a mobile health setting. The goal of the pilot study implementation and evaluation is to apply lessons learned to more effective HIV prevention evidence and programming.

**Results:**

The combination HIV prevention package in this protocol includes (1) offering HIV testing and counseling for all youth; (2) voluntary medical circumcision and condoms for males; (3) pre-exposure prophylaxis (PrEP), conditional cash transfer (CCT), and contraceptives for females; and (4) referrals for HIV care among those identified as HIV-positive. The combination package platform selected is mobile health teams in an integrated services delivery model. A cross-sectional analysis will be conducted to determine the uptake of the interventions. To determine long-term impact, the protocol outlines enrolling selected participants in mutually exclusive longitudinal cohorts (HIV-positive, PrEP, CCT, and HIV-negative) followed by using mobile phone text messages (short message service, SMS) and in-person surveys to prospectively assess prevention method uptake, adherence, and risk compensation behaviors. Cross-sectional and sub-cohort analyses will be conducted to determine intervention packages uptake.

**Conclusions:**

The literature review, focus groups, and modeling indicate that offering age- and gender- specific combination HIV prevention interventions that include biomedical, behavioral, and structural interventions can have an impact on HIV risk reduction. Implementing this protocol will show the feasibility of delivering these services at scale. The MP3 Youth study is one of the few combination HIV prevention intervention protocols incorporating youth- and gender-specific interventions in one delivery setting. Lessons learned from the design of the protocol can be incorporated into the national guidance for combination HIV prevention for youth in Kenya and other high-burden SSA settings.

**Trial Registration:**

ClinicalTrials.gov NCT01571128; http://clinicaltrials.gov/ct2/show/NCT01571128?term=MP3+youth&rank=1 (Archived by WebCite at http://www.webcitation.org/6nmioPd54)

## Introduction

Nearly three decades into the epidemic, sub-Saharan Africa (SSA) remains the region most heavily affected by human immunodeficiency virus (HIV), with nearly 70% of the 34 million people living with HIV globally residing in the region [1-4]. Youth aged 15 to 24 years bear the highest burden of new infections, and in SSA, account for 80% of the 1.9 million new infections each year [5,6]. Young females are twice as likely as their male counterparts to be infected [4,6], making females 15 to 24 years in SSA the most at-risk group for HIV infection. The incidence and prevalence of HIV among youth in SSA remains high [4] and literature shows that programs for youth are often vertical, uncoordinated, and not evidence-based [7,8]. The delivery of proven interventions needs to account for the complexity of the interconnected drivers of HIV, especially among youth, necessitating combination prevention packages relevant to the target population(s). We set out to develop a protocol for a cross-sectional and longitudinal pilot study of a sex- and gender-specific combination HIV prevention approach in western Kenya for youth called “MP3 Youth.” The focus of this paper is to outline the development details of the protocol, which includes a multi-method approach for designing a pilot study of combination HIV prevention.

### HIV in Kenyan Youth

The study setting for this protocol is Kenya, where national HIV prevalence is 5.6% among individuals aged 15 to 49 years [9,10]. With the exception of the Nyanza Province where the study will take place, HIV prevalence in Kenya has declined [9-11]. The prevalence of HIV varies markedly by region, and ranges between 2% to 15% (Figure 1) [11,12]. Children and youth aged 0 to 24 years represent 55.6% of Kenya’s population [12] and surveillance data indicates that most new HIV infections occur among youth 15 to 24 years of age [11,12]. Females between the ages of 20 to 24 have a risk of HIV infection, four times higher than males of the same age [10-12]. The 2012 Kenya AIDS indicator Survey (KAIS) shows that nationally the prevalence of HIV among females aged 15 to 19 is 1.1%, a reduction from the 3.5% reported in 2007. The HIV prevalence for females aged 20 to 24 years is 4.6% (previously 7.5%) [12]. The prevalence of HIV among males is much lower than females of the same age group. HIV prevalence among males aged 15 to 19 and 20 to 24 years old is 0.9% and 1.3%, respectively [10,11].

**Figure 1 figure1:**
[figure not shown]
Map of HIV prevalence in Kenya (KAIS, 2014).

### Theoretical Basis for Combination HIV Prevention Package

The evidence-based methodology for the MP3 Youth combination intervention protocol is guided by a multi-theoretical approach grounded in social ecological theory (Figure 2) [13,14]. The combination prevention approach needs to address behavioral, biomedical, and structural levels, and tailor interventions to address each level according to age and sex. MP3 Youth focuses on the context in which an individual finds him or herself socially and physiologically. The prevention framework includes reducing health risks associated with age, gender, and biological susceptibility. HIV prevention requires not only equipping youth with knowledge, skills, risk perception, condoms, and positive social norms, but also instituting systems change [15]. Systems change includes policies that prioritize youth sexual and reproductive health across sectors. MP3 Youth builds upon these psychosocial determinants of HIV prevention and consolidates the prominent themes into the MP3 Youth framework. The social ecological theory guides MP3 Youth to address the gender-specific risks across this broad spectrum of factors from individual to structural (including economic factors) [13,14]. The final package of interventions to be selected for inclusion in the protocol meets all aspects of the social ecological framework.

The interventions will be offered in a mobile health setting. Mobile health events involve determining an appropriate place in the community and setting up a temporary health center using vans, tents, or other temporary structures. Mobile events are effective for reaching rural and other hard-to-reach populations. The mobile health setting will take into account the socio-political and community context of the participants. This context will drive the location, time, and manner in which the interventions are offered.

The four aims of the MP3 Youth study are shown in Textbox 1. Each of the aims has specific analytic objectives and outcomes. This paper will focus on the development of the objectives and outcomes for Aim 3 (the pilot study). We hypothesize that by strategically designing and piloting a gender- and youth-specific combination HIV prevention intervention, we can learn important lessons about scaling up combination prevention to curb the HIV epidemic among young people.

Aims of the MP3 Youth study.AimAim 1: Select a package of interventions by identifying epidemiologic targets for HIV prevention among youth in sub-Saharan Africa through a systematic review, meta-analysis, and qualitative data collection.Aim 2: Perform mathematical modeling for selection of interventions with the highest population impact.Aim 3: Develop a protocol and implement a pilot study of a gender-specific combination HIV prevention package for youth (aged 15 to 24) in western Kenya.Aim 4: Derive lessons from the pilot for future combination HIV prevention evaluations.

**Figure 2 figure2:**
[figure not shown]
Social ecological framework (Centers for Disease Control and Prevention, 2013).

## Methods

MP3 youth is a mixed-methods study incorporating quantitative, qualitative, and modeling approaches, and capturing cross sectional and longitudinal data elements. A multi-method process was undertaken to design the MP3 Youth combination HIV prevention pilot study protocol (Aim 3) (Figure 3). To determine the most effective evidence-based interventions for youth HIV prevention in SSA, we first conducted a systematic review of the literature. In addition to the evidence, the study collects formative data through focus groups to determine the knowledge, attitudes, and preferences of youth about which interventions are most acceptable, as well as by whom and where they would like them to be delivered. Mathematical modeling will be used to determine the impact of the interventions, considering coverage and adherence levels, as well as to determine the most cost-effective combination of interventions (Figure 3). All of these methods are useful for determining the best “package” of gender-specific interventions during the intervention design phase. The steps for developing the multi-method protocol for the field pilot study (Aim 3) are outlined below.

**Figure 3 figure3:**
[figure not shown]
MP3 Youth Study Design Schematic.

### Aim 1: Review and Selection of Package Components Procedures

To develop the protocol, our team compiled a priori knowledge of what drivers may be most important to target for HIV prevention among SSA youth (Figure 4). These include early initiation of sex, lack of circumcision, alcohol abuse, power structure (intergenerational sex, gender violence), lack of HIV serostatus knowledge, low contraceptive use, and high rates of unintended pregnancy. Our approach was to understand not just modifiable drivers of HIV transmission among youth, but also to lay out a replicable strategy for assessing whether there were sufficient evidence-based interventions to address each driver. We constructed a framework with “strength of evidence” thresholds to determine whether to include specific interventions in the combination package for the protocol.

**Figure 4 figure4:**
[figure not shown]
Key drivers of youth HIV risk in sub-Saharan Africa.

#### Systematic Review

The development of the combination package included a systematic review and meta-analysis where we conducted a systematic review using standardized procedures [16]. The review question (gender-specific modifiable drivers of the epidemic and evidence-based interventions among youth) yielded a critical base of evidence that fed into the development of the focus group discussions, the mathematical modeling, and the overall protocol design. While a detailed account of the methods and results of the systematic review will be reported in a separate publication, they were mentioned here to show the groundwork for the pilot study protocol elements.

#### Focus Group Discussions

The development of this protocol includes an appreciation of the sociocultural and community context in which youth experience. Community context is critical to a comprehensive protocol that will lead to successful pilot study implementation. To assess the acceptability of the components in the pilot study protocol, we collected qualitative data using focus groups with youth and community leaders to assess HIV risk and protective factors and the best location and format for the delivery of the combination prevention interventions. Topic guides for these groups were informed by the systematic review and key stakeholders. The detailed methods and results of the focus group discussion will be outlined in a separate publication. The description of this aim here is intended to illustrate the foundation upon which the pilot study protocol was built.

### Aim 2: Mathematical Modeling for Component Selection

Components from the systematic review and focus group discussions were fed into the development of a mathematical model that was used to triangulate the appropriateness and potential effectiveness of the interventions to be included in the pilot study protocol. Results of the systematic review and epidemiologic analyses were used to provide the modeling parameters. Mathematical modeling was used to assist in selecting components of intervention packages most likely to have complementary or synergistic effects. The modeling provided estimated impact and costs of strategies that focus interventions on different sub-populations according to sex, age, risk behavior, and other factors. An appropriate model structure was agreed upon following detailed consultations with the study team and reviews of the modeling literature. The model incorporated sex- and age- specific coverage to long-term interventions and risk compensation that could undermine intervention package efficacy over time. The model was designed, constructed, solved, and analyzed using modern computational software (MathWorks, MATLAB) using techniques developed by Hallett et al [17]. A user-friendly toolkit was built using MATLAB and several stakeholders were trained on how to use the modeling tool for intervention selection and program planning.

The model will be continuously updated with information generated during the implementation of the pilot study to produce more refined and robust projections of both impact and cost-effectiveness. Model projections were fed into study design considerations in Aim 3 (pilot study) and Aim 4 (the effectiveness trial). The full details of the methods and results of the modeling will be reported in another paper. The inclusion of the modeling here is intended to show the process for finalizing the component selection of a combination HIV prevention package described in depth in this protocol.

### Aim 3: Pilot Study

The previous aims were completed to inform Aim 3 of this protocol. This section provides an overview of setting, participants, and details of how interventions can be implemented and how data should be collected. Our preliminary research confirmed that there were numerous examples of individual HIV prevention interventions aimed at addressing the drivers of the HIV epidemic among youth [18-30]. Many of the vertically-focused single interventions were efficacious, but there remained a need for combination approaches [8]. The studies reviewed as part of the systematic review informed our decision about the most effective and feasible components to include in the protocol for the combination package. These components are HIV testing and counseling (HTC) [31,32], condoms [33,34], family planning (contraception) [35,36], voluntary medical male circumcision [37-39], conditional cash transfers (CCTs) [40-44], pre-exposure prophylaxis (PrEP) [40,45,46], and HIV care and treatment [47,48]. All interventions included in the protocol to be offered as part of MP3 Youth were chosen because they were efficacious, youth-friendly, possible to implement in a mobile health setting, and potentially sustainable following the MP3 Youth study.

#### MP3 Youth Package

Based on results of the first two aims, the gender-specific MP3 Youth package was developed (Figure 5). The tailoring of interventions to specific individuals is referred to as the “MP3 Youth package of services.” For all participating youth, the package will include HIV counseling and testing. For all HIV-positive participants, the package will include point of care cluster of differentiation 4 (CD4) and viral load testing, and facilitated linkage to care (n is approximately 100), including prevention of mother-to-child transmission for pregnant females. For all participating males, the package will also include condoms and voluntary medical male circumcision, whereas for all participating females the package will also include contraception (both male and female condoms) and family planning. PrEP will be included for HIV-negative, out-of-school females while CCT will be included for HIV-negative, in-school females. The protocol aims for approximately 1000 youth to be enrolled in the pilot study and from these, sub-cohorts of youth (approximately 300) will be followed up prospectively for 12 months to document behaviors and adherence related to selected interventions. In addition, follow-up by phone to approximately 100 youth who are HIV negative at baseline will assess whether or not they were HIV retested over the last 12 months or if they are willing to be retested at the 12-month follow-up period.

The combination MP3 Youth package menu options will be delivered through community-based mobile health teams and all interventions will be offered on-site. PrEP and CCT cohort enrollment will also be initiated on site and followed-up prospectively off-site. Mobile health teams will be able to select the most appropriate location within a community to set up tents to deliver the MP3 Youth packages. Mobile health events increase accessibility to the interventions and reduces stigma by offering it in the context of a health event where other youth-friendly services are also being provided [32,49].

**Figure 5 figure5:**
[figure not shown]
MP3 Youth packages.

#### Study Objectives

The objectives of the pilot study were developed based on the formative stages of the protocol development by an expert panel that recognized the gaps that this study could fill. The primary objective is to determine the feasibility and acceptability of a pilot combination HIV prevention package specific for female and male youth (MP3 Youth) in Homa Bay County, Nyanza Province, Kenya. This will be determined by examining uptake and coverage of the intervention package among youth. The secondary objectives are (1) to examine adherence to HIV care including antiretroviral therapy (ART) among HIV-positive males and females 15 to 24 years of age; (2) to evaluate the feasibility of offering PrEP to high HIV risk out-of-school females 18 to 24 years of age and to contribute data to the current question of how best to initiate and support ongoing adherence for females using PrEP; (3) to assess the feasibility of delivering CCT to keep girls in school over the 12 months; and (4) to evaluate school attendance over 12 months of CCT cohort participants. For the logic model, see Multimedia Appendix 1.

#### Setting

The mobile health events for intervention delivery are proposed to be held in Homa Bay County, Nyanza Province, Kenya using the infrastructure of our community partner Impact Research and Development Organization (IRDO).

#### Participants and Sample Size

In the cross-sectional portion of the study, we plan to enroll approximately 1000 youth (ages 15 to 24) over the course of 10 mobile events, held for 7 to 10 days each. We plan on enrolling a sub-section of the enrolled participants into longitudinal cohorts (approximately 300 youth).

The pilot study is not meant to provide a definitive test of the combination package efficacy. Nevertheless, power calculations can provide an idea of the magnitude of temporal effects on ART adherence or school attendance that could be reliably detected using conventional tests of significance. Assuming at least an 80% retention rate at the 12-month follow-up, a minimum of 40 CCT cohort participants, 40 PrEP cohort participants, and 80 HIV-positive cohort participants will contribute data for all planned assessments. A paired-samples *t* test with 80 pairs can detect a difference in means of one-third of a standard deviation (*d*=.33) with 83% power. A paired-sample *t* test with 40 pairs can detect a difference in means of *d*=.45, 80% power.

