### Target Sample Size

As stated previously, the MP3 Youth package will be offered to approximately 1000 youth who attend the mobile events. These participants will be part of the cross-sectional analyses. In addition, a subset of youth will be enrolled in longitudinal cohorts. The cohorts and their corresponding sample sizes are shown in Textbox 3.

Cohorts and sample sizes.CohortsHIV-positive cohort:All participants who test HIV positive (including participants who report being positive at baseline and are retested) during all mobile events will be invited to enroll in the longitudinal cohort using SMS/USSD surveys to collect data.Participants will be given mobile phones.The target HIV-positive sample size is approximately 100.Conditional cash transfer (CCT) cohort:In-school girls between 15 to 24 years of age who test HIV negative will be screened for eligibility at each of the mobile events.The target CCT sample size is approximately 50.Pre-exposure prophylaxis (PrEP) cohort:Out-of-school girls who test HIV negative and are between 18 and 24 years of age will be screened for eligibility at each of the mobile events.Participants will be given mobile phones.The target PrEP sample size is approximately 50.HIV-negative cohort:A random selection of participants who test HIV negative at the mobile events will be asked to complete one follow-up phone call at 12 months to assess willingness and intention to undergo HIV retesting (no study phone will be provided).The target sample size is approximately 100.

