## Results

Quantitative data analysis will be conducted using Stata software [67] and R statistical software [68]. Initial analyses will involve inspecting frequency distributions to identify outlying values and skewed variables requiring transformation. Descriptive analyses will provide means, medians, or prevalence of risk factors with associated confidence intervals. Analytic comparisons of pilot cohort drop-outs versus retained subjects will be done using multivariate analysis of variance (MANOVA) for normally distributed continuous variables with log10 (X+1) transformations on skewed behavioral variables, and chi-square tests for categorical variables and Wilcoxon tests for ranked data, with significance levels adjusted for multiple testing.

For the PrEP, CCT, and HIV-positive cohorts, changes over time in risk behaviors will be estimated focusing on initial change (baseline vs 6 months) and delayed change or persistence of initial effects (6 months vs 12 months). We anticipate minimal missing data due to use of CAPI and SMS/USSD data. The primary goal of the longitudinal cohorts is to provide data needed to describe the feasibility of PrEP, ART, and CCT, including medication adherence and school attendance over time. Levels of and changes in adherence and school attendance will be presented graphically, for example, with box plots at each assessment point and trajectory plots. For a detailed analysis plan, see Multimedia Appendix 2.

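### The counts of 40, 40 and 80 are month-12 retention figures, not participants with data at every assessment, and the multiplicity-adjusted attrition tests are insensitive to selective loss within a cohort

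*Protocol article*

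**What the plan says.** Participants and Sample Size starts from a retention assumption, "Assuming at least an 80% retention rate at the 12-month follow-up", and draws from it that "a minimum of 40 CCT cohort participants, 40 PrEP cohort participants, and 80 HIV-positive cohort participants will contribute data for all planned assessments". It then gives the power of a paired t test: "test with 80 pairs can detect a difference in means of one-third of a standard deviation" with 83% power, and 40 pairs can detect d = 0.45 with 80% power.

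The enrolment targets are in Target Sample Size: "The target HIV-positive sample size is approximately 100", "The target CCT sample size is approximately 50" and "The target PrEP sample size is approximately 50".

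Cohort Follow-Up Schedules sets four follow-ups for the CCT and HIV-positive cohorts (months 3, 6, 9 and 12) and eight for the PrEP cohort (months 1 to 6, 9 and 12).

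The analysis text under Results names two contrasts for change in risk behaviours in these three cohorts: baseline versus month 6, and month 6 versus month 12. It also says "We anticipate minimal missing data due to use of CAPI and SMS/USSD data". Drop-outs are to be compared with retained subjects by MANOVA, chi-square tests and "Wilcoxon tests for ranked data, with significance levels adjusted for multiple testing".

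**The concern.** Being present at month 12 is a condition on one visit. Having data at all planned assessments is a condition on every visit. The second cannot be more frequent than the first, and the two are equal only if no retained participant misses an earlier wave. The article goes from one to the other without any allowance, and calls the result a minimum. Anyone sizing a contrast that involves month 6 would take the number of pairs as assured when it is not.

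The attrition check raises a separate problem. Multiplicity adjustment protects against false alarms. When the question is whether those who left differ from those who stayed, the costlier error is to miss a real difference, and adjustment makes that error more likely. The article describes the cohorts' main purpose as describing adherence and school attendance over time. If those who leave adhere or attend less, which is plausible though not something the article states, the description would be too favourable, and a non-significant check would not reveal it.

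**Working it through.** **Inputs from the article.** Targets 100, 50 and 50; retention 80%; d = 0.33 with 80 pairs and d = 0.45 with 40 pairs; the follow-up schedules and contrasts given above. **Assumed, because not stated:** two-sided alpha 0.05; response at month 6 among those retained at month 12; 5 to 10 attrition tests with Bonferroni adjustment; one variable compared at a time.

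**1. Where the counts come from.** 100 × 0.80 = 80 and 50 × 0.80 = 40. Nothing is deducted for missed intermediate assessments.

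**2. The article's own power.** Paired t test, noncentrality d√n, n − 1 degrees of freedom:
- n = 80, d = 0.33: noncentrality 2.95, power 83.0% (stated 83%).
- n = 40, d = 0.45: noncentrality 2.85, power 79.3% (stated 80%; the normal approximation gives 81.2%).

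Both figures reproduce. Baseline versus month 12 (for example CD4 and viral load in the HIV-positive cohort) needs only month-12 retention beyond baseline, so 80 and 40 pairs are right for it.

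**3. Month 6 versus month 12.** Pairs = target × 0.80 × r, where r is the proportion of those retained who also respond at month 6.

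| r | pairs (target 100) | power, d = 0.33 | pairs (target 50) | power, d = 0.45 |
|---|---|---|---|---|
| 1.00 | 80 | 83% | 40 | 79% |
| 0.95 | 76 | 81% | 38 | 77% |
| 0.90 | 72 | 79% | 36 | 75% |
| 0.80 | 64 | 74% | 32 | 69% |

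Baseline versus month 6 is not fixed by month-12 retention in either direction. Some retained participants may miss month 6, and some later drop-outs may still be present then.

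**4. Sensitivity of the attrition check.** At 80% retention, the comparison is 10 drop-outs with 40 retained (CCT or PrEP), or 20 with 80 (HIV-positive). Two-sample t test, noncentrality d√(n₁n₂/(n₁+n₂)), n₁ + n₂ − 2 degrees of freedom. At a true difference of 0.5 SD:

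| drop-outs v retained | noncentrality | alpha 0.05 | 0.05/5 = 0.01 | 0.05/10 = 0.005 |
|---|---|---|---|---|
| 10 v 40 | 1.41 | 28% | 11% | 7% |
| 20 v 80 | 2.00 | 51% | 27% | 20% |
| 40 v 160 (three cohorts pooled) | 2.83 | 80% | 59% | 50% |

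The smallest difference detectable with 80% power is 1.01 SD unadjusted and 1.25 to 1.35 SD adjusted for 10 v 40. For 20 v 80 it is 0.71 SD and 0.87 to 0.93 SD.

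**The case against.** Five points can be made for the article.

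- **The power statement is sound.** A paired test needs two waves, not all of them. One can compute far smaller numbers with data at every wave (for instance 19 to 28 of 50 in the PrEP cohort, if each earlier wave is answered independently by 90 to 95%) and infer that the stated power collapses. The documents do not support that. The response rates and their independence are invented, and all-wave completeness does not determine a two-wave contrast. The article offers its power figures for ART adherence and school attendance, and attendance is also verified at the schools, so a missed interview need not lose it. This objection stands.
- **Few missing data and 20% loss can coexist.** A reader might call these a contradiction. The reason given is the electronic collection tools, which fits skipped items within a completed survey, and the preceding paragraph treats drop-outs separately. It is an ambiguity. Those tools do not prevent a whole text survey from going unanswered, so the sentence needs limiting.
- **The attrition check is not powerless.** The number of tests, the adjustment and any pooling are unstated, and MANOVA is a joint test that the calculation above does not model. Pooled, a 0.8 SD difference would be found with 95% power even at alpha 0.005; the HIV-positive cohort alone has 89% unadjusted. To say that the tests cannot detect attrition would therefore be too strong. What remains is low sensitivity to moderate differences within a cohort.
- **Missing-data handling may be set out elsewhere.** The article does not say that only those who stayed are analysed, or that a non-significant check will be read as reassurance. It refers to Multimedia Appendix 2, which is not at hand, so the lack of a mixed model or missing-data method in the article is no finding.
- **The study is a pilot.** It is declared not to be a definitive test of efficacy, and its primary outcomes (coverage, enrolment, uptake, satisfaction) are mainly measured at the mobile events. This limits the severity.

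**Conclusion.** Two statements need correction. First, 40, 40 and 80 are month-12 retention counts. At 80% retention they are an upper bound on the number with data at all planned assessments and cannot be presented as the minimum. The power figures are correct for the pair counts used and for baseline versus month 12. For month 6 versus month 12 the loss is about 2 to 5 percentage points if 90 to 95% of those retained respond at month 6, and about 9 to 10 points at 80%. Those response rates are assumptions.

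Second, adjusting the attrition tests for multiplicity makes a weak check weaker. Within one cohort, at 0.5 SD, power is 28% or 51% unadjusted and 7 to 11% or 20 to 27% adjusted, under an assumed 5 to 10 Bonferroni tests. A non-significant result would not show that attrition is ignorable.

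Severity is minor: neither correction changes the design or the stated power for its own pair counts.

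**What to change.** 1. In Participants and Sample Size, describe 40, 40 and 80 as the numbers expected to be retained at month 12, and drop the claim that they have data at all planned assessments. Give the expected pairs for each planned contrast (baseline versus 6, 6 versus 12, baseline versus 12), with the month-6 response assumption stated.
2. Under Results, restrict the expectation of minimal missing data to skipped items within completed surveys, so that it does not appear to cover missed waves or drop-out.
3. Replace the multiplicity-adjusted attrition tests with standardised differences and 95% confidence intervals for drop-outs versus retained subjects, reported by cohort. With 10 versus 40, the half-width near zero is about 1.96 × √(1/10 + 1/40) = 0.69 SD, and with 20 versus 80 it is 1.96 × √(1/20 + 1/80) = 0.49 SD. The reader then sees directly how large a difference the data cannot exclude.

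The cost is somewhat smaller stated pair counts for month 6 versus month 12 and a little more reporting. No extra data or participants are needed.
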